### Sample size

A sample size of 270 in each group will have 80% power to detect a 10% reduction in the rates of extubation failure from 25% in the n-CPAP group to 15% in the n-BiPAP group at a 0.05 two-sided significance level. A 10% reduction in extubation failure rate would be clinically significant and could support a change in practice to using n-BiPAP as first line treatment post-extubation. Existing meta-analyses of trials comparing NIPPV and n-CPAP had around 80 babies in each arm.

### Recruitment

Some preliminary written and oral information will, whenever possible, be offered to parents prior to birth if the baby is likely to be eligible. Additional information will be given once the baby has been born. Informed written consent will be sought from a parent only after they have been given a full oral and written explanation of the study.

Sufficient time will be provided for consent. In most circumstances it will be possible to provide 24 hours time for parents to make their decision. Occasionally, babies may be ready to come off the ventilator quickly. Under those circumstances less time may be available for parents to decide. Since both treatments are used in routine care we anticipate that this will not place parents under undue pressure.

Where there is sufficient time between recruitment and randomisation, parents will be offered an early appointment with the Principal Investigator or delegated deputy who will meet with them to ensure that they understand the trial procedures and continue to consent to participate in the trial. At all stages it will be made clear to the parents that they remain free to withdraw their baby from the study at any time.

Parents who do not speak English will only be approached if an adult interpreter is available. Trust interpreter and link worker services will be used to support involvement of participants whose first language is not English.

A senior investigator will be available at all times to discuss concerns raised by parents or clinicians during the course of the trial. [name], Service User representative will also be available to talk to parents who require further information from another parent who has experience in participating in research.

Information about the study will continue to be offered to parents after their infant leaves the unit. A newsletter about the study will be disseminated at regular intervals.

### Randomisation

Infants will be randomised following the decision to extubate. Block randomisation will be used, stratified by centre and gestation (< 28 weeks or ≥ 28 weeks). Web based randomisation will be used.

### Blinding

The n-BiPAP device produces an audible noise which cannot be masked. Due to this, parents, clinicians involved in patient care and researchers assessing study end-points will not be blinded to the nature of the study treatments. To reduce bias, criteria for extubation and re-intubation have been defined and will be strictly adhered to.

### Minimisation of bias

This is an un-blinded randomised controlled trial. To minimise bias 'Criteria for extubation' and 'Criteria for failure of extubation' have been carefully defined. These will be strictly adhered to throughout the trial. Randomisation will be conducted once the decision to extubate has been taken. The time duration between randomisation and extubation will be closely monitored and explanations sought where there is undue delay. Auditing will also be done on adherence to 'Criteria for extubation' and 'Criteria for failure of extubation' during site visits.

### Criteria for extubation

These will be:

(1) Loaded with caffeine according to standard local protocol (and)

(2) Satisfactory blood gases defined as pH of more than 7.25 and partial pressure of carbon dioxide of less than 7 kPa (52.5 mmHg). As most babies will not have arterial access at the time of extubation we have not defined partial pressure of oxygen in targeted blood gas indices (and)

(3) Mean airway pressure of 7 cm water or less (and)

(4) Fractional inspired oxygen concentration of 35% or less (and)

(5) Good spontaneous respiratory effort, persistently higher than ventilator rate.

### n-CPAP

The n-CPAP group will receive at extubation a single level continuous positive airway pressure of 6 cm water for at least 48 hours before weaning is commenced. If the infant is stable for the preceding 24 hours defined by having fewer than three minor apnoeas and no increase in oxygen requirement, weaning will be permitted. Minor apnoea will be defined as apnoea requiring stimulation but not mask ventilation. CPAP will be decreased from 6 cm water by 1 cm water every 48 hours if tolerated based on the above criteria. This will be done until a pressure of 4 cm water is reached. If a pressure of 4 cm water is successfully tolerated for 48 hours then time off n-CPAP will be allowed. Thereafter, no fixed weaning regime based on number of hours in a day the infant will be allowed to come off CPAP will be prescribed.

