### Secondary outcome measures

(1) Maintenance of successful extubation for 7 days from the hour of extubation

(2) Total days on ventilator, n-CPAP/n-BiPAP (anytime requiring respiratory support during a 24 hour clock will be counted as a day).

(3) Number of ventilator days following first extubation attempt (anytime requiring respiratory support during a 24 hour clock will be counted as a day).

(4) Oxygen requirement at 28 days of age and at 36 weeks' corrected gestation

(5) pH, partial pressure of carbon dioxide in the first post extubation gas

(6) Duration of hospitalisation

(7) Rates of abdominal distension requiring cessation of feeds for 7 days post extubation

(8) Rate of apnoea and bradycardia expressed as events per hour during the 48 hours following extubation

(9) Age at transfer back to referral centre in days

(10) Adverse events as described later

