### n-BiPAP

The n-BiPAP group will receive at extubation a mean airway pressure of 6 cm water (positive end expiratory pressure of 4 cm water and peak inspiratory pressure of 8 cm of water). Inspiratory time of one second and respiratory rate of 30/min will always be maintained. If the infant is stable for the preceding 48 hours at mean airway pressure of 6 cm water defined by having fewer than 3 minor apnoeas and no increase in oxygen requirement, weaning will be permitted. Minor apnoea will be defined as apnoea requiring stimulation but not mask ventilation.

The infant will then receive a mean airway pressure of 5 cm water (positive end expiratory pressure of 4 cm water and peak inspiratory pressure of 6 cm of water). If the infant is stable for the preceding 48 hours at mean airway pressure of 5 cm water defined by having fewer than 3 minor apnoeas and no increase in oxygen requirement, weaning will be permitted. Minor apnoea will be defined as apnoea requiring stimulation but not mask ventilation.

The infant will then receive a CPAP of 4 cm water. If the infant is stable for the preceding 48 hours at CPAP of 4 cm water defined by having fewer than 3 minor apnoeas and no increase in oxygen requirement, then time of CPAP will be permitted. Minor apnoea will be defined as apnoea requiring stimulation but not mask ventilation. Thereafter, no fixed weaning regime based on number of hours in a day the infant will be allowed to come off CPAP will be prescribed.

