### Duration of study

540 infants will be recruited over 2.5 years. The trial will terminate when the last recruited infant is discharged from hospital or dies.

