## Trial status

Ethics Committee approval was granted on 4^th ^January 2011. Recruitment has commenced on 1^st ^July 2011.

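### At the first two weaning steps the same stability limit covers 24 hours on n-CPAP but 48 hours on n-BiPAP, which can lengthen n-BiPAP time in the support-days outcome

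*Protocol article*

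**What the plan says.** The n-CPAP section keeps infants at 6 cm water for at least 48 hours. Weaning is then allowed "If the infant is stable for the preceding 24 hours defined by having fewer than three minor apnoeas and no increase in oxygen requirement". The next reduction follows the same test: "CPAP will be decreased from 6 cm water by 1 cm water every 48 hours if tolerated based on the above criteria".

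The n-BiPAP section sets the same count and the same oxygen condition over twice the period. From the first level the condition begins "If the infant is stable for the preceding 48 hours at mean airway pressure of 6 cm water", and from the second "If the infant is stable for the preceding 48 hours at mean airway pressure of 5 cm water". If it is met, "weaning will be permitted". Minor apnoea is defined identically in both arms, and no reason is given for the different windows.

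At 4 cm water both arms are most naturally read as needing 48 hours under the same criteria. That step is not in question.

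The second item under Secondary outcome measures is "Total days on ventilator, n-CPAP/n-BiPAP (anytime requiring respiratory support during a 24 hour clock will be counted as a day". Under Data collection, ventilation and apnoeas are recorded daily for one week after extubation.

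**The concern.** Both arms spend at least 48 hours at each of the first two levels, so the minimum schedule is the same. What differs is the hurdle for leaving each level. Three minor apnoeas within 48 hours hold an n-BiPAP infant back. An n-CPAP infant with the same three, two on the first day and one on the second, may wean. The oxygen condition also runs over 24 hours against 48 and works in the same direction.

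The arms therefore differ in weaning rule as well as in mode of support. If n-BiPAP infants show more days of non-invasive support, part of the excess could come from the rule. If n-BiPAP truly shortens support, part of that benefit could be hidden. A comparison of total support days cannot by itself tell these apart.

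**Working it through.** **Inputs from the protocol.** The limit is at most two minor apnoeas. The window is 24 h (n-CPAP) or 48 h (n-BiPAP). The minimum stay is 48 h per level, with two steps (6 to 5 and 5 to 4 cm water). The protocol states no figure for this point, so there is none to reproduce.

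**Assumed input.** The minor apnoea rate L per day is not in the protocol. I take 0.25 to 2 per day, Poisson, equal in both arms.

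**Direction.** The 48 h window contains the 24 h window, so an infant who passes the n-BiPAP test also passes the n-CPAP test, and not the reverse. As an average rate, the limit is under 3 per day on n-CPAP and under 3/2 = 1.5 per day on n-BiPAP.

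**Chance of passing one check at 48 h.** P(X ≤ 2) = e^(−m)(1 + m + m²/2), with m = L for 24 h and m = 2L for 48 h. At L = 1:
- n-CPAP: e^(−1) × 2.5 = 0.920
- n-BiPAP: e^(−2) × 5 = 0.677

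**Infants held beyond the 4-day minimum.** This is 1 − P². At L = 1 it is 1 − 0.846 = 15% on n-CPAP and 1 − 0.458 = 54% on n-BiPAP.

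| L per day | Pass one check, n-CPAP v n-BiPAP | Held beyond 4 days, n-CPAP v n-BiPAP |
|---|---|---|
| 0.25 | 99.8% v 98.6% | 0.4% v 2.9% |
| 0.5 | 98.6% v 92.0% | 3% v 15% |
| 1 | 92.0% v 67.7% | 15% v 54% |
| 1.5 | 80.9% v 42.3% | 35% v 82% |
| 2 | 67.7% v 23.8% | 54% v 94% |

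**Extra n-BiPAP time over the two steps.** In simulation, each infant moves at the first review, after at least 48 h at the level, with at most two apnoeas in the window. Review is hourly in both arms, or hourly on n-BiPAP with n-CPAP decided only every 48 h. The last two columns let rates vary between infants (gamma, variance half the squared mean) and fall 5 to 10% a day.

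| L per day | Constant rate, hourly | Constant rate, n-CPAP 48-hourly | Varying and falling, hourly | Varying and falling, n-CPAP 48-hourly |
|---|---|---|---|---|
| 0.25 | 0.02 | 0.01 | 0.02–0.03 | 0.01–0.02 |
| 0.5 | 0.1 | 0.07 | 0.12–0.18 | 0.07–0.11 |
| 1 | 0.7 | 0.4 | 0.6–0.8 | 0.3–0.5 |
| 1.5 | 1.9 | 1.1 | 1.2–1.8 | 0.6–1.0 |
| 2 | 4.1 | 2.6 | 1.9–3.1 | 1.0–1.8 |

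Entries are days. At L = 1 with hourly review and a constant rate, the mean two-step times are 4.74 days (n-BiPAP) and 4.06 days (n-CPAP), a gap of about 0.7. Once-daily review in both arms would give larger gaps (0.20 day at 0.5 per day, 1.2 at 1 per day). I do not rely on that case.

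These are times at which weaning is first allowed. Infants who are re-intubated and leave the ladder are not modelled.

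**The case against.** **The size is unproven.** This stands. Nothing in the protocol shows an average of 1 minor apnoea per day or more, and all infants are loaded with caffeine before extubation. The 4.1-day figure needs two apnoeas every day at a constant rate common to all infants. The infants most likely to leave the ladder are plausibly those with high rates.

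**The gap may be lost in the noise.** This stands in part. The SD of support days is not given. With assumed SDs of 5, 10 or 20 days, the standard error of the difference is SD × √(2/270) = 0.43, 0.86 or 1.72 days. A 0.7-day gap is then 1.6, 0.8 or 0.4 standard errors. The outcome also counts whole days, so a gap of 0.2 day or less will usually leave an infant's count unchanged.

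**Weaning is only permitted, and each arm has its own ladder.** This does not remove the asymmetry. Discretion can delay weaning in either arm, but it cannot release an n-BiPAP infant who fails the 48-hour test, because the protocol defines compliance as full adherence. A fixed 24-hour delay after permission in both arms leaves the gap essentially unchanged. The comparison could be read as mode plus schedule, but the protocol does not say so. The rule does work against the trial's hypothesis, so it cannot create a shorter n-BiPAP time.

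**The data could separate rule from mode.** This is partly right. A reader might infer that they cannot do so at all, but the daily records go some way. The two steps need at least 4 days, so they fall within the recorded week unless an infant is long delayed. The check is partial: it ends at day 7, daily records only approximate a rolling window, and it shows eligibility rather than what would have happened.

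**Conclusion.** The asymmetry is real, unexplained and confined to the 6-to-5 and 5-to-4 cm water steps. At equal apnoea rates it makes the n-BiPAP rule stricter and can lengthen n-BiPAP time. In the cases relied on, the gap is at most about 0.2 day at 0.5 apnoeas per day or below and about 0.3 to 0.8 day at 1 per day. It is larger above that. All these figures rest on assumed Poisson rates equal in the two arms.

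Two stronger readings are not supported. A reader might infer that the primary outcome is biased, but it covers the first 48 hours after extubation and neither arm weans before then. A reader might also infer that support days are distorted by the full ladder gap. Ladder time does not carry over one-for-one, because weaning is discretionary once permitted and no schedule is prescribed for time off CPAP after 4 cm water.

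The point is worth acting on because a listed outcome is compared under different rules and the correction is small. It does not threaten the trial's main conclusion.

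**What to change.** Amend the n-CPAP or the n-BiPAP section so that one look-back window, 24 or 48 hours as the clinical investigators choose, applies at both steps in both arms for infants still to be recruited. Record for each infant which rule version applied.

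For infants weaned under the present rule, or for all infants if it is kept, state with the support-days result that the comparison is not like for like. From the first-week daily records, tabulate when each infant first met a 24-hour and a 48-hour criterion. This needs the form to identify apnoeas requiring stimulation. The same records, pooled over arms, would show which apnoea rate applies.

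The cost is a short amendment, a site memo and one data flag. The real downside is two weaning rules within the trial, since Trial status reports "Recruitment has commenced on" 1 July 2011. By publication on 9 December 2011, 161 days had passed. Under Duration of study, "540 infants will be recruited over 2.5 years", about 913 days, so 161/913 = 17.6%. With even recruitment (an assumption) that is 0.176 × 540 ≈ 95 infants. Approval and roll-out time would raise the number, but most infants could still be weaned under one rule.

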### n-BiPAP

The n-BiPAP group will receive at extubation a mean airway pressure of 6 cm water (positive end expiratory pressure of 4 cm water and peak inspiratory pressure of 8 cm of water). Inspiratory time of one second and respiratory rate of 30/min will always be maintained. If the infant is stable for the preceding 48 hours at mean airway pressure of 6 cm water defined by having fewer than 3 minor apnoeas and no increase in oxygen requirement, weaning will be permitted. Minor apnoea will be defined as apnoea requiring stimulation but not mask ventilation.

The infant will then receive a mean airway pressure of 5 cm water (positive end expiratory pressure of 4 cm water and peak inspiratory pressure of 6 cm of water). If the infant is stable for the preceding 48 hours at mean airway pressure of 5 cm water defined by having fewer than 3 minor apnoeas and no increase in oxygen requirement, weaning will be permitted. Minor apnoea will be defined as apnoea requiring stimulation but not mask ventilation.

The infant will then receive a CPAP of 4 cm water. If the infant is stable for the preceding 48 hours at CPAP of 4 cm water defined by having fewer than 3 minor apnoeas and no increase in oxygen requirement, then time of CPAP will be permitted. Minor apnoea will be defined as apnoea requiring stimulation but not mask ventilation. Thereafter, no fixed weaning regime based on number of hours in a day the infant will be allowed to come off CPAP will be prescribed.

### Standards of care

Routine hourly monitoring of heart rate, peripheral oxygen saturation and respiratory rate will be performed. Delivered n-CPAP and n-BiPAP pressures will be monitored regularly. Efforts will be made to maintain desired CPAP and mean airway pressure levels in accordance with standard nursing practice.

### Criteria for failure of extubation

This will be defined as:

(1) Uncompensated respiratory acidosis defined as pH less than 7.2 and partial pressure of carbon dioxide of more than 8 kPa (60 mmHg) (or)

(2) Major apnoea requiring mask ventilation

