### Primary outcome measure

Failure of extubation during the first 48 hours post-extubation will be used as the primary outcome measure. 48 hours will be calculated from the hour of extubation. Failure of extubation has been defined later under 'Criteria for failure of extubation'. We have chosen 'Failure of extubation' as our primary outcome measure to maintain similarity with previous trials conducted using NIPPV. We will also measure the following secondary outcome measures.

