### Data collection

All data for trial analysis are routine clinical items that can be obtained from the clinical notes. Data will be collected on trial-specific case report forms. Data will be entered by the research nurse or Local principal investigator on a web based electronic case record form provided by OpenCDMS. Access to the form will be password protected and participants will be identified by trial number only.

Clinical information will be collected at the following times:

1. At trial entry: Information on eligibility; background information and randomisation

2. Following randomisation: Daily observations regarding ventilation, vital signs, blood gases, haemoglobin and C-reactive protein, apnoeas and de-saturations for 1 week after extubation

3. Follow-up: Data on duration of hospital stay, duration of oxygen requirement, oxygen requirement at 28 days and at 36 weeks corrected gestational age and age at transfer back to referral centre, total number of days on ventilator, n-CPAP and n-BiPAP

Further information will be collected on expected serious adverse events. No additional blood samples are required for this study.

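### One of the two primary-outcome criteria can be detected only on a blood gas, and the safeguards for this open-label trial do not cover whether or when gases are taken in each arm

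*Protocol article*

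**What the plan says.** The Primary outcome measure section states: "Failure of extubation during the first 48 hours post-extubation will be used as the primary outcome measure". Criteria for failure of extubation gives two criteria joined by an or. The first is "Uncompensated respiratory acidosis defined as pH less than 7.2 and partial pressure of carbon dioxide of more than 8 kPa (60 mmHg". The second is "Major apnoea requiring mask ventilation".

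On blinding, "parents, clinicians involved in patient care and researchers assessing study end-points will not be blinded to the nature of the study treatments". The stated protection is: "To reduce bias, criteria for extubation and re-intubation have been defined and will be strictly adhered to". Minimisation of bias adds an audit of adherence to those criteria at site visits.

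On measurement, Standards of care says "Routine hourly monitoring of heart rate, peripheral oxygen saturation and respiratory rate will be performed", and the only other monitoring it names is of delivered pressures. Data collection says that all analysis data are routine items from the clinical notes, and that "No additional blood samples are required for this study". It lists blood gases among the observations recorded daily for a week after extubation, without times or numbers. Secondary outcome 5 is "pH, partial pressure of carbon dioxide in the first post extubation gas", also without a time.

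**The concern.** A numeric threshold removes judgement about a value once it exists. It does not remove judgement about whether the value is obtained. An infant who is acidotic but not sampled, and who has no major apnoea, complies fully with the criteria and counts as a success. An audit of adherence would find nothing wrong.

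The article sets no times and adds no samples, so the natural reading is that staff who know the allocation decide when a gas is taken. If one arm is sampled more often, or at more telling moments, its recorded failure rate can rise without any true difference. Under Rescue treatment, meeting the criteria leads to mechanical ventilation. A difference in detection would therefore carry into seven-day extubation success and ventilator days as well.

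Secondary outcome 5 has a related gap. On one reading of its wording, an infant re-intubated for apnoea before any gas would contribute a gas taken on the ventilator, which does not reflect the allocated support.

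**Working it through.** **The plan's own figure.** Sample size gives 25% versus 15%, 80% power, two-sided 0.05 and 270 per group.

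- Without continuity correction: n = [1.96 × √(2 × 0.20 × 0.80) + 0.842 × √(0.25 × 0.75 + 0.15 × 0.85)]² / 0.10² = 250.
- With continuity correction: (250/4) × [1 + √(1 + 4/(250 × 0.10))]² = 270, which matches.
- At 270 per arm, power is 83.0% without the correction and 80.1% with it. The sample size is not in question. The calculations below use the uncorrected normal approximation.

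**Inputs that the documents do not give (assumptions).**

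- s, the share of failures that occur by acidosis alone: 0.3, 0.5 or 0.7.
- d, the fraction of those detected on a gas within 48 hours: 1 in one arm, and 0.9 or 0.8 in the other.

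**Model.** Observed rate = true rate × (1 − s + s × d). With a true rate of 25% in both arms, the spurious difference is 25 × s × (1 − d) points. For s = 0.5 and d = 0.8 the observed rates are 25.0% and 25 × (0.5 + 0.4) = 22.5%, a gap of 2.5 points. That is 270 × 0.025 = 6.75 infants in one arm.

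The rejection probability is Φ[(Δ − 1.96 × SE₀)/SE₁] + Φ[(−Δ − 1.96 × SE₀)/SE₁], where SE₀ is the pooled and SE₁ the unpooled standard error. In the same example SE₀ and SE₁ are both about 0.0366. The two terms are 0.1006 and 0.0041, which sum to 0.1047.

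| Missed in one arm | s | Spurious difference (points) | Two-sided false-positive rate |
|---|---|---|---|
| 10% | 0.3 | 0.75 | 5.5% |
| 10% | 0.5 | 1.25 | 6.3% |
| 10% | 0.7 | 1.75 | 7.6% |
| 20% | 0.3 | 1.5 | 6.9% |
| 20% | 0.5 | 2.5 | 10.5% |
| 20% | 0.7 | 3.5 | 16.1% |

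**Opposite direction.** Suppose the true rates are 25% and 15%, and 20% of acidosis-only failures are missed in the n-CPAP arm only. Power falls from 83.0% to 70.8%, 60.8% and 49.8% for s = 0.3, 0.5 and 0.7.

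**Equal under-sampling.** With equal true rates there is no false difference. With true rates of 25% and 15%, s = 0.5 and d = 0.8 in both arms, the observed rates are 22.5% and 13.5%, and power is 77.9%.

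**The case against.** The strongest reply is that this is partly an argument from silence. A journal article condenses a fuller protocol, and gas timing could well sit in that document, the case report forms or the site training. Standards of care is a short paragraph, not a complete monitoring schedule. Data collection lists blood gases among daily observations for a week, with no distinction by arm, so gases are evidently expected in both arms throughout the 48 hours. Both modes are described as being in routine use, which weakens any claim that staff would watch one more closely.

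Much of this stands, and it limits the point. It does not remove it. Daily recording fixes neither the number nor the timing of gases, and the article states positively that it uses routine data with no extra samples.

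A reader might infer three stronger things that the documents do not support:

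- **That acidosis is half of the primary outcome.** It is one of two criteria, and its share of failures is not stated.
- **That the illustrated differences estimate the bias.** No gap in sampling is documented, and no direction is implied. Some infants missed at first would be sampled later or meet the apnoea criterion, which shrinks the effect.
- **That the analysis can do nothing about it.** If the gases are logged, differential ascertainment can be shown and examined.

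The reply is also right that imposing common gas times is not free. It could require extra samples, which the article rules out. It could alter management, because meeting the criteria triggers ventilation. It would also change ascertainment after recruitment began on 1 July 2011.

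**Conclusion.** The point holds in a limited form. One of the two failure criteria depends on a gas being taken, allocation is known to those treating and assessing, and the stated safeguards act only after a gas result exists. The article therefore has no stated protection against the arms differing in how often or when gases are taken.

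The effect is modest at the low end of the illustration and material at the high end: 0.75 to 3.5 points, or 7.5% to 35% of the 10-point target, with a false-positive rate of about 5.5% to 16%. These figures rest wholly on the assumed acidosis share, on the assumed one-arm loss, and on missed cases never being counted later. They show that the gap can matter at this sample size, not that it will.

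**What to change.** 1. **Data collection.** For every gas in the 48 hours after extubation, in both arms, record the time, sample route, reason and respiratory support at that moment.
2. **Reporting.** Give the number and timing of gases by arm to the Data Monitoring Committee and in the results.
3. **Statistical analysis.** Pre-specify a sensitivity analysis of the primary outcome for differential ascertainment. One example is failure by major apnoea or re-intubation within 48 hours, analysed apart from acidosis found on a gas. Re-intubations prompted solely by a gas should be identifiable, because they share the same dependence on sampling.
4. **Timing.** Where sites' routine gases allow, align their timing across arms, without adding samples and without changing the failure thresholds or clinical management.
5. **Secondary outcome 5.** Define it as the first gas taken while the infant is still on non-invasive support. Pre-specify how infants re-intubated before any such gas are handled, for example ranked worst in an ordinal model, a model type that the Statistical analysis section already allows.

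The cost is a few form fields and modest extra analysis. Items 1 to 3 and 5 need no extra samples and do not touch care. Item 4 is conditional for the reasons given under the objection. Because recruitment has started, gases from infants already enrolled would have to be recovered from the notes as far as these allow.
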